#### Stopping rules

Two stopping rules are specified: (1) expected success and (2) futility. At each planned interim analysis *k*=1,2,...,*K*, let $n_{i}^{k}$ denote the number of participants in arm *i* who have reached the primary endpoint by the time of interim *k*. Let $y_{i}^{k}$ denote the number of participants in arm *i* out of $n_{i}^{k}$ who met the primary outcome criteria, and *D*_*k*_ denote the available data. In addition to the participants with observed outcomes at interim *k*, there are $m_{i}^{k}$ participants enrolled in arm *i*, of which some unknown $\tilde w_{i}^{k}$ will have a future response. There are also $l_{i}^{k}$ participants who could still be enrolled into arm *i* (in 1:1 allocation up to maximum sample size) of which some unknown $\tilde z_{i}^{k}$ will have a future response.

Using the prediction model and primary analysis model, the following values are calculated 
$$\begin{aligned} \text{PPoS}_{k}^{0}(q) &= \mathbb E_{\tilde w_{1}^{k},\tilde w_{2}^{k}|y_{1}^{k},y_{2}^{k}}\left[\mathbf{1}_{(q,1]}\left\{\mathbb P\left(\delta<0|y_{1}^{k},y_{2}^{k},\tilde w_{1}^{k},\tilde w_{2}^{k}\right)\right\}\right] \\ \text{PPoS}_{k}^{1}(q) &= \mathbb E_{\tilde w_{1}^{k},\tilde w_{2}^{k},\tilde z_{1}^{k},\tilde z_{2}^{k}|y_{1}^{k},y_{2}^{k}}\left[\!\mathbf{1}_{(q,1]}\left\{\mathbb P\left(\delta<0|y_{1}^{k},y_{2}^{k},\tilde w_{1}^{k},\tilde w_{2}^{k},\tilde z_{1}^{k},\tilde z_{2}^{k}\right)\right\}\right]. \end{aligned} $$

The decision rule used for recommendations at interim analyses (assuming at least some number of participants are still to be enrolled to achieve the maximum sample size) is 
$${}d(D_{k})=\left\{\begin{array}{ll} \text{stop for expected success} & \text{if}\ \text{PPoS}_{k}^{0}(q) > \overline{c}_{k} \\ \text{stop for futility} & \text{if}\ \text{PPoS}_{k}^{1}(q) < \underline{c}_{k} \\ \text{continue to analysis }k+1 &\text{otherwise} \end{array}\right. \quad k=1,...,K $$ where $q=0.95, \overline {c}_{k}=0.95$, and $\underline {c}_{k}=0.05$ for all *k* which were selected based on simulations (see Operating characteristics).

### Analysis of secondary outcomes

#### Clinical and mechanistic

Based on the intention-to-treat (ITT) and per-protocol (PP) analysis sets, the proportion of participants with each clinical and mechanistic outcome response will be reported. Unadjusted posterior summaries for the difference in proportions between the study vaccine and comparator will be calculated using beta-binomial models as for the primary outcome. Adjusted analyses will use logistic regression models where posterior summaries of the adjusted odds ratio associated with receiving the study vaccine will be reported along with any other model parameters. These models will adjust for the same covariates as in the adjusted model for the primary outcome and use the same priors.

#### Laboratory—stage 1 atopic immunophenotypic response

The sensitivity of the assay for total IgE and antigen-specific IgE concentrations will be reported. Results outside the limits of detection will be reported as below or above the limit of quantification. For analyses of concentrations, measurements will be log_10_ transformed from the unit scale and concentrations outside detection limits will be treated as censored.

For each outcome, we will report by treatment group and visit for the stage 1 assay analysis sets the following descriptive summaries: 
The median, IQR, and range of concentrationsThe proportion of missing concentrationsThe proportion of concentrations below or above limits of quantificationThe proportion of concentrations exceeding the positive response threshold (see page 38)Kaplan-Meier plots of concentrations

Inferences for geometric mean concentrations (GMC) and geometric mean ratios (GMR) between study groups will assume censored normal regression models for log-concentrations. Univariate models will be fit for each visit with treatment-specific means, and a multivariate model for all visits with unstructured covariance matrices and visit by treatment-specific means. If issues arise with the covariance structure, a simpler covariance model will be assumed, such as heterogeneous compound symmetry. Priors on mean parameters will be normal with mean 0 and standard deviation 10. An LKJ(1) prior is specified on the correlation matrix, and half-Cauchy with location 0 and scale 10 on the marginal standard deviation parameters. If the assumptions of the censored regression model are inappropriate then two-part models may be considered to separate modelling of detection and concentration at each visit.

Inferences for relative proportions exceeding positive response threshold by study group will assume logistic regression models with a fixed term for treatment group, visit, and their interaction, and random intercepts for participants.

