Maternal receipt of pertussis booster vaccination in the preceding pregnancy (yes/no) and type of pertussis-containing vaccine givenMaternal receipt of pertussis booster vaccination in the preceding 5 years (not including preceding pregnancy) (yes/no)Maternal seasonal influenza vaccination during preceding pregnancy (yes/no)Family history of atopic diseases: 
At least one first degree relatives with any clinician diagnosed atopic disease (asthma, allergic rhinitis, atopic dermatitis, IgE-mediated food allergy, no family history of atopy)Physical examination at enrolment: 
Temperature (Celsius scale)Weight (grammes)Length (cm)Head circumference (cm)

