### Adjusted analysis

A secondary supportive analysis of the primary outcome will use logistic regression to estimate a covariate adjusted odds ratio associated with the study vaccine strategy. The prognostic baseline covariates to be included as fixed effects are: 
SexStudy siteBreastfeeding status (exclusively, partially, or not fed with breast milk in the week before enrolment)Birth order (first born versus subsequent birth order)Combined parental income (≤ $18,000, $18,001 to $37,000, $37,001 to $87,000, $87,001 to $180,000, > $180,000)Mode of delivery (Cesarean section versus not Cesarean section)Family history of atopic disease (first degree relative with food allergy versus not)

We will specify weakly informative Student *t*priors for regression coefficients with 4 degrees of freedom, 0 mean, and standard deviation of 1.75. Inference will be based on Markov chain Monte Carlo (MCMC) samples.

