#### Laboratory—stage 1 and 2 vaccine response

The sensitivity of each assay will be reported. Results outside the limits of detection will be reported as below or above the limit of quantification. For analyses of concentrations, measurements will be log_10_ transformed and concentrations outside the detection limits will be treated as censored.

For each outcome, we will report by treatment group and visit for the stage 1 and stage 1+2 (PT only) assay analysis sets: 
The median, IQR, and range of concentrationsThe proportion of missing concentrationsThe proportion of concentrations below the limit of quantificationThe proportion of concentrations exceeding the seroprotective/seropositivity thresholds (see page 38)The proportion of participants with a 4-fold or greater increase in their concentration from 18 to 19 monthsKaplan-Meier plots of concentrations

Inferences for GMC, GMR, and proportions will use the same modelling approach as for the atopic immunophenotypic response outcomes.

Non-inferiority of the wP vaccine strategy compared to the standard aP vaccine strategy with respect to PT will be assessed against a non-inferiority margin of 2/3 on the GMR [18]. That is, if the GMR for a particular antigen and visit is defined as 
$$\text{GMR} = \frac{\text{GMC}_{\text{wP}}}{\text{GMC}_{\text{aP}}} $$ then non-inferiority will be evaluated according to 
$$\mathbb P\left(\text{GMR}\geq \frac{2}{3}\Big\vert \text{data}\right). $$

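### The vaccine-antibody models carry no baseline covariate, so a small gain in precision from maternal pertussis booster status, already collected, is left unused in the pertussis-antigen GMRs

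*SAP article*

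**What the plan says.** The SAP article sets out the concentration models under the stage 1 atopic immunophenotypic response. They are censored normal regressions on log10 concentration. For single visits the text reads "Univariate models will be fit for each visit with treatment-specific means". The joint model that accompanies these is described as "a multivariate model for all visits with unstructured covariance matrices and visit by treatment-specific means". No baseline covariate is named. The section on stage 1 and 2 vaccine response then says: "Inferences for GMC, GMR, and proportions will use the same modelling approach as for the atopic immunophenotypic response outcomes". In that section PT "will be assessed against a non-inferiority margin of 2/3 on the GMR", and "then non-inferiority will be evaluated according to" the posterior probability that the GMR is at least 2/3. No cut-off for that probability is given.

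The clinical outcomes are treated differently. Under Adjusted analysis the primary outcome gets a supportive logistic model, introduced by "The prognostic baseline covariates to be included as fixed effects are" and a list of seven items. Maternal booster is not among them. For the clinical secondary outcomes, "These models will adjust for the same covariates as in the adjusted model for the primary outcome and use the same priors".

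The baseline data listed under Baseline characteristics include "Maternal receipt of pertussis booster vaccination in the preceding pregnancy (yes/no", together with the type of vaccine given and confirmation on the immunisation register where possible. The only use stated for this item is descriptive.

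**The concern.** The article plans covariate-adjusted models for the clinical outcomes and none for the antibody outcomes, and it gives no reason for the difference. Yet the antibody models are where adjustment is simplest. In a linear model on the log scale, adding a baseline covariate leaves the target GMR unchanged. In a logistic model, adjustment changes the odds ratio being estimated.

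Maternal pertussis vaccination in pregnancy is a natural candidate for the pertussis antigens. Randomisation is stratified by site only, so booster status is not balanced by design, and the stage 1 set has only about 75 infants per arm.

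PT-specific IgG around the 18-month booster is a secondary outcome named in the abstract, and PT is the only antigen with a non-inferiority margin. Precision also has a practical side: stage 2 blood sampling may end before its cap of 300 participants if non-inferiority is shown sooner. A tighter GMR could, in principle, shorten it.

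**Working it through.** **The plan's own figure.** There is none to reproduce. The article gives no SD, sample-size calculation, power or decision cut-off for the antibody comparison.

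**Inputs from the article.**
- Margin 2/3 on the GMR, so the distance from a true GMR of 1 is log10(1.5) = 0.1761.
- 1:1 allocation. Stage 1 has 150 infants, or 75 per arm.
- Stage 2 sampling runs up to 300 participants. It is not clear whether the 300 includes the 150, so the pooled PT set is 300 or 450, that is 150 or 225 per arm.

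**Assumed inputs.**
- Booster coverage c = 0.8.
- Titre ratio r between booster groups of 0.5, 0.7 or 0.85.
- Total log10 SD of 0.35 or 0.5.
- True GMR of 1.
- Cut-off 0.95 on the posterior probability, treated as one-sided 5% (z = 1.645).
- No loss of information from censoring.

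**Step 1: variance explained.** For a yes/no covariate, R² = c(1−c)·(log10 r)²/SD². With c = 0.8, c(1−c) = 0.16. With r = 0.5, (log10 r)² = 0.0906, so the numerator is 0.0145.
- SD 0.5: R² = 0.0145/0.25 = 0.058.
- SD 0.35: R² = 0.0145/0.1225 = 0.118.
- r = 0.7: R² = 0.015 (SD 0.5) or 0.031 (SD 0.35).
- r = 0.85: R² = 0.003 or 0.007.

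**Step 2: chance of showing GMR ≥ 2/3.** This is Φ(0.1761/(s·√(2/n)) − 1.645), with s = SD unadjusted and s = SD·√(1−R²) adjusted.

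Example with n = 75, SD 0.5, r = 0.5:
- Unadjusted: 0.1761/(0.5 × 0.1633) = 2.157, and Φ(0.512) = 0.696.
- Adjusted: s = 0.5 × √0.942 = 0.485, giving 0.1761/(0.485 × 0.1633) = 2.222, and Φ(0.577) = 0.718.

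| n per arm | SD | r | Unadjusted | Adjusted |
|---|---|---|---|---|
| 75 | 0.5 | 0.5 | 0.696 | 0.718 |
| 75 | 0.5 | 0.7 | 0.696 | 0.701 |
| 75 | 0.5 | 0.85 | 0.696 | 0.697 |
| 75 | 0.35 | 0.5 | 0.92 | 0.95 |
| 150 | 0.5 | 0.5 | 0.920 | 0.933 |
| 150 | 0.5 | 0.7 | 0.920 | 0.923 |
| 225 | 0.5 | 0.5 | 0.982 | 0.986 |
| 225 | 0.5 | 0.7 | 0.982 | 0.983 |

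The SD must be the same in both steps. The larger R² of 0.118 belongs with SD 0.35, where the unadjusted chance is already 0.92. It cannot be combined with the 0.70 that holds at SD 0.5.

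**Step 3: wider ranges.** With coverage 50–90%, ratio 0.8 to 0.5 and SD 0.3–0.5, R² runs from 0.3% to 25%. The standard error falls by 1 − √(1−R²), that is by 0.2% to 13%. At 80–90% coverage and a ratio of 0.67 or closer to 1, R² is about 0.3–5% and the standard error falls by less than 3%. If the true GMR is 0.8, with 150 per arm and SD 0.5, an R² of 5% moves the chance from 0.392 to 0.406.

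**The case against.** The strongest reply is that the article never calls maternal booster prognostic for antibody. It uses that word only for the primary-outcome covariates, which leave booster out. Coverage, titre ratio and SD all come from outside the document. That stands: the gain is conditional on assumptions, and any maternal effect may be weaker at 18 and 19 months than at 6 and 7 months.

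A reader might infer that the PT comparison is biased or wrongly analysed. The documents do not support this, because the unadjusted GMR is valid under randomisation and no passage contradicts another here.

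A reader might also infer that a stage term is needed because PT data are pooled across stages. Nothing in the article shows that PT levels differ by stage. The assay infants in both stages come from one site, and 1:1 allocation in blocks of 6 to 10 should keep the arms nearly balanced within each stage.

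Extending a pertussis-booster covariate to the IgE models, or to the pneumococcal, hepatitis B and Hib models, has no rationale in the document either.

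Finally, the article's own hierarchy makes the unadjusted analysis of the primary outcome primary and the adjusted one supportive. Consistency with it does not require the adjusted GMR to decide non-inferiority. It does support adding an adjusted model and saying beforehand which result counts. What survives these objections is that a low-cost covariate is already collected and is unused for the pertussis antigens.

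**Conclusion.** The point holds as a modest efficiency improvement on a secondary outcome. The IgG models, including the one behind PT non-inferiority, contain treatment and visit means only, while a plausible predictor of pertussis antibody is recorded and used only descriptively.

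Under the most favourable ratio examined (0.5) at 80% coverage, the gain in the stage 1 set is two to three percentage points. In the pooled PT set at SD 0.5 it is about one point or less, and for ratios nearer 1 it almost vanishes. All of these sizes rest on the assumed coverage, ratio, SD, true GMR and 0.95 cut-off. It would go too far to read the PT comparison as underpowered for want of this covariate, because the article gives no figures from which its power could be derived.

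**What to change.** Before unblinding, add to the section on vaccine response:
- Maternal pertussis booster in this pregnancy (yes, no, unknown) enters as a fixed effect in the log10 concentration models for PT, FHA and PRN only.
- Adjusted and unadjusted GMRs are both reported.
- One of the two is named in advance as the GMR that gives the PT non-inferiority probability.

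A stage term in the pooled PT model may be added as an optional safeguard, with no gain shown for it. The cost is a few sentences in the SAP and at most two extra coefficients per single-visit model. No new data are needed.

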#### Laboratory—stage 1 and 2 vaccine response

The sensitivity of each assay will be reported. Results outside the limits of detection will be reported as below or above the limit of quantification. For analyses of concentrations, measurements will be log_10_ transformed and concentrations outside the detection limits will be treated as censored.

For each outcome, we will report by treatment group and visit for the stage 1 and stage 1+2 (PT only) assay analysis sets: 
The median, IQR, and range of concentrationsThe proportion of missing concentrationsThe proportion of concentrations below the limit of quantificationThe proportion of concentrations exceeding the seroprotective/seropositivity thresholds (see page 38)The proportion of participants with a 4-fold or greater increase in their concentration from 18 to 19 monthsKaplan-Meier plots of concentrations

Inferences for GMC, GMR, and proportions will use the same modelling approach as for the atopic immunophenotypic response outcomes.

Non-inferiority of the wP vaccine strategy compared to the standard aP vaccine strategy with respect to PT will be assessed against a non-inferiority margin of 2/3 on the GMR [18]. That is, if the GMR for a particular antigen and visit is defined as 
$$\text{GMR} = \frac{\text{GMC}_{\text{wP}}}{\text{GMC}_{\text{aP}}} $$ then non-inferiority will be evaluated according to 
$$\mathbb P\left(\text{GMR}\geq \frac{2}{3}\Big\vert \text{data}\right). $$

### Safety and tolerability outcomes

The number and proportions of infants in each study group with each type of solicited AE and their intensity grading will be summarised for each day following vaccination (day 0 to 6) for each vaccine occasion (2, 4, 6, and 18 months in stage 1; 2 and 18 months in stage 2). The number and proportion of infants in each study group with each type of solicited AE, and at least one type of solicited AE for each vaccine occasion will be reported.

### Vaccine satisfaction

The responses for vaccination satisfaction of primary caregivers for infants in each study group on the 5-point Likert scale on day 7 after each vaccine occasion will be summarised by counts and proportions. The number of vaccination experiences reported as either unsatisfactory or very unsatisfactory on the Likert scale will be reported by study group as counts and proportions.

### Subgroup analyses

No pre-specified subgroup analyses will be undertaken; however, some subgroup effects may be investigated as part of post hoc analyses. Any such subgroup analyses will be noted as being post hoc.

### Missing data

Reasons for missingness will be summarised. Patterns and predictors of missingness will also be investigated and summarised. Descriptive and summary statistics will generally be based on complete-cases data. The primary analyses will be based on complete-cases. Secondary analyses using multiple imputation for missing responses and covariates will be undertaken to investigate sensitivity of the results.

### Sensitivity analyses

Sensitivity of results to the specified priors will be investigated by estimating parameters under different prior configurations than those used in the primary analyses. In particular, the hyperparameter for prior variances will be varied to assess how conclusions may change under varying strength of the prior.

### Software

All data cleaning, summaries, and exploratory and pre-specified analyses will be undertaken using R [19]. For models where MCMC sampling is required, we will use Stan [20].

### Reporting

Results for the stage 1 atopic immunophenotypic response, vaccine response, and safety and tolerability outcomes will be reported by study group once complete follow-up has been obtained for the 150 participants in stage 1 up to their 7-month visit. This will not include SAEs or unsolicited AEs.

## Operating characteristics

The operating characteristics of the OPTIMUM trial were estimated using Monte Carlo methods assuming various scenarios for the data generating process.

The final thresholds were selected informally on the basis of their type I error, type II error, and expected sample size. For example, based on the final row of Fig. 1, tresholds consistent with type I error of approximately 0.05 were identified. These threshold combinations were then assessed for power and expected sample size, noting that many combination options result in similar opearting characteristics. Due to the common use of 0.95 as a one-sided threshold, the value *q*=0.95 was selected.

**Fig. 1 Fig1:**
[figure not shown]
Probability of deciding superiority at the final analysis by decision thresholds and effect size assuming constant 16 per week accrual

### Scenarios

A first interim analysis is scheduled to occur when primary endpoint data is available on 200 subjects. Subsequent interim analyses occur after every additional 200 subjects with available endpoint data until a stopping rule is met, or enrolment is already complete at the maximum sample size of 3,000.

Trial data was generated allowing variations in accrual rate and pattern of accrual, time to primary endpoint, true response probability in the control and treatment arms, and decision thresholds (Table 2).

Accrual was assumed to follow a non-homogeneous Poisson process and we investigated varying the baseline rate and varying the shape of accrual by allowing for slow initial accrual and a ramp-up in the latter stages of the trial. We assumed baseline accrual of 16 per week, and 5 per week (slow accrual is worst case for false positives), and a gradually increasing rate of accrual.

Time to primary outcome was assumed to be uniform between 48 and 72 weeks (mean 60 weeks) post-randomisation.

The probability of food-allergy within the standard aP vaccine strategy, $\theta _{a}^{\star }$, and study wP vaccine strategy, $\theta _{w}^{\star }$, populations investigated were $\theta _{a}^{\star }=0.1$ and $\theta _{w}^{\star }\in \{0.05, 0.06, 0.07, 0.08, 0.09,0.1\}$. Data were generated as Bernoulli random variables using the specified probability with time of enrolment generated from the accrual specification, and time to response generated from the time to outcome specification.

A grid of decision threshold values was investigated across all scenarios. For the final analysis, posterior probability thresholds of *q*∈{0.95,0.955,0.96,0.965,0.97} were investigated. Futility thresholds were fixed across all interim analyses and set to $\underline {c}\in \{0,0.025,0.05,0.075,0.1, 0.2\}$. Expected success thresholds were fixed across all interim analyses and set to $\overline {c}\in \{0.8,0.9,0.925,0.95,0.975,1\}$.

### Results

Simulation results from all scenario combinations were based on 10,000 replications performed using R [19]. Results are presented here only for the 16 per week accrual scenario; the other scenarios are available in a supplemental file (Additional file 1). The R functions and scripts used to simulate the trials and summarise the results are available at https://github.com/[name]/OPTIMUMsims.

Figures 1 and 2 present the probability of deciding superiority at the final analysis (power) and expected sample size respectively over the grid of effect sizes and decision thresholds assuming constant accrual of 16 participants per week. Figures 3 and 4 present marginal stopping probabilities for expected success and futility respectively.

**Fig. 2 Fig2:**
[figure not shown]
Expected sample size by decision thresholds and effect size assuming constant 16 per week accrual

**Fig. 3 Fig3:**
[figure not shown]
Marginal stopping probability for expected success by stage, effect size, and thresholds assuming constant 16 per week accrual and futility bound $\underline {c}=0.05$

